**M.3. Pregnancy:**

M.3.a. If a patient becomes pregnant during the Lead-in Phase, treatment will be stopped and she will not be eligible for the Randomized Phase of the trial.

M.3.b. If a patient becomes pregnant during the Randomized Phase, treatment will be discontinued for the duration of the pregnancy. Treatment may be resumed three months post-partum if the patient is not breast feeding.

M.3.c. If a male patient's partner(s) becomes pregnant during the Lead-in Phase, ribavirin will be stopped, but not peginterferon alfa-2a. The male patient and his pregnant partner will be advised to use a barrier method of contraception for the remainder of the pregnancy, and post-partum if the male patient's partner is breast feeding.

**N. ADVERSE EVENTS**

**N.1. Definition**

N.1.a. An adverse event is any adverse change from the patient's baseline (pre-treatment) condition, including intercurrent illness which occurs during the course of the trial, after the consent form has been signed, whether the event is considered related to treatment or not.

N.1.b. A serious adverse event is an untoward medical occurrence that results in any of the following:

1. Death
2. Is life threatening (risk of death at the time of the event).
3. Requires in-patient hospitalization or prolongation of existing
4. hospitalization
5. Results in persistent or significant disability/incapacity
6. Congenital abnormality or birth defect

Important medical events that do not result in one of the events listed above may be considered a serious adverse event when, based upon appropriate medical judgment, they may jeopardize the patient and may require medical or surgical intervention to prevent one of the outcomes listed above.

N.1.c. A serious adverse event which is unexpected and is drug related (even remotely) will require expedited reporting (see N.3.a.).

N.1.d. The following events are trial outcomes and will not be considered to be serious adverse events:

1. Development of HCC or presumed HCC
2. A CTP score of 7 or higher at 2 consecutive study visits

3. Ascites
4. Variceal hemorrhage
5. Hepatic encephalopathy
6. Spontaneous bacterial peritonitis

N.2. Data collection procedures for adverse events

N.2.a. At each follow-up visit through Month 54, patients will be interviewed regarding medical conditions, medical changes, and symptoms that have occurred since the last visit. An Adverse Event form will be completed if any adverse event is reported. If the Study Coordinator or Principal Investigator learns of any hospitalizations or other adverse events between study visits, an Adverse Event form will be completed. All adverse events and Serious Adverse Events as of May 1, 2007 will not be reported to the DCC.

N.2.b. A Serious Adverse Event form will be completed for all adverse events rated as serious.

N.2.c. Patients will be followed for all ongoing unresolved adverse events until they are either resolved, or in the opinion of the Principal Investigator, the patient is medically stable.

N.3. Reporting procedures

N.3.a. All serious adverse events, for patients in both the treated and the control group will be reported to the DCC and to Roche within 24 hours by telephone. The Serious Adverse Event form will be faxed to the DCC and Roche within 24-48 hours. This reporting includes serious adverse events that occur from the time the patient has signed the Screening or Trial informed consent to study visit Month 54 (6 month post Trial follow-up). Serious adverse events on patients who are in the control arm of the Randomized Phase and have stopped treatment for 12 weeks or patients who have not yet received treatment need to be reported only to the DCC. Roche will review all serious adverse events and will notify the DCC if an event is considered to be unexpected. The DCC will distribute the expedited report to NIDDK, the FDA, the DSMB, and clinical centers.

Status reports on serious adverse events will be generated by the DCC and sent to the DSMB every month and will include the relationship of the adverse event to trial medications, the severity of the event and if the event is resolved or ongoing. Adverse events will be reported annually to the FDA, as required.

N.3.b. All deaths, in both the treated and in the control group will be reported to the DCC within 24 hours by telephone. The Death Report will be faxed to the DCC within 24 hours. This reporting begins at the time the patient has signed the Trial informed consent up to the last scheduled patient visit (through October 2009). The report will include the relationship of the death to trial medications. A Clinical Outcome form will also be completed and sent to DCC for distribution and review by the Outcome Review Board (ORB). Deaths will be reported immediately to NIDDK and the DSMB. A death

will be reported in an expedited report only if it is unexpected and drug related. A death must also be reported in accordance with local law and regulations.

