#### A.2. Overview:

Up to 1800 patients who meet the inclusion and exclusion criteria (Sections E and F) will be entered into a Lead-in Phase. They will be treated with a combination of peginterferon alfa-2a and ribavirin for a period of 24 weeks. Patients who have no detectable HCV RNA at week 20 will continue on combination treatment until week 48. Patients who do not clear virus will be randomized 50:50 at week 24 to receive either peginterferon alfa-2a alone or no further therapy for the next three and a half years. Nine hundred patients will be randomized and both randomized groups will be monitored quarterly during these 42 months. Biopsies for these patients will be obtained at 24 and 48 months after the start of the Lead-in Phase.

In August, 2001, to increase enrollment two modifications were made to the study design: Those Week 20 Responder patients with virologic breakthrough or relapse documented by detection of HCV RNA at weeks 36, 48, 60 or 72, and those patients who are adequately treated with pegylated interferon and ribavirin combination therapy outside of the HALT-C Lead-in (Express Group) will be considered for randomization into the maintenance phase. These patients will be followed for an additional 48 months and their biopsies performed 18 months and 42 months after randomization.

All treatment in the randomized phase will end in January 2007. A small number of patients may not have completed 48 months at that time. Every patient will stop treatment at that time point, regardless of what month of randomization they are in. Those patients who complete Month 48 will be offered an "extended follow-up" visit after their Month 54 study visit at Month 60 and Month 72 through April 2007. These visits will primarily be to identify outcome events, and to provide information to patients concerning the current status of the trial. Some questionnaires, blood tests, and an ultrasonogram will be performed. This visit is not to take the place of patients establishing a relationship with a primary care or liver specialist physician once the Month 54 visit is completed.

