**K. OUTCOME VARIABLES**

K.1. Primary Outcome Variables

The major outcome variable used in this study will be progression of liver disease as judged by any of the following outcomes:

K.1.a. Increase in Ishak fibrosis score by 2 points or more at 2 or 4 year biopsies

K.1.b. Death from any cause

K.1.c. Development of HCC

K.1.d. CTP score of 7 or higher at two consecutive study visits

K.1.e. Variceal hemorrhage

K.1.f. Ascites

K.1.g. Spontaneous bacterial peritonitis

K.1.h. Hepatic encephalopathy

K.2. Secondary Outcome Variables

Secondary outcome variables will include:

K.2.a. Quality of life,

K.2.b. Serious adverse events, and

K.2.c. Events requiring dose reductions (in both treatment groups).

K.2.d. Changes in fibrosis from baseline at year 2 or year 4 biopsy.

K.2.e. Presumed Hepatocellular Carcinoma

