P.2.c. Baseline characteristics that form continuous variables will be compared using analysis of variance or t-tests. Data will be transformed (e.g. logarithms) prior to analysis if transformation is needed to meet the assumptions of normality and homogeneity of variances that underlie these methods. Non-parametric methods, such as the Wilcoxon test, will be used if data fail to meet these assumptions even after transformation (172).

P.2.d. Characteristics that form ordinal categorical variables, (e.g., Child-Turcotte-Pugh score, biopsy severity scores) may be compared using analysis of variance or t-tests if the number of categories is large enough for the data to approximately fit the assumption of normality. Otherwise non-parametric methods or methods for categorical data will be used. Categorical variables (e.g., presence or absence of cirrhosis) will be analyzed using chi-square tests (173,174).

P.2.e. It is expected, due to randomization, that the patients in the treatment arm will, on average, be similar with respect to variables that might influence outcome. However, for imbalances that persist despite randomization, co-variables or strata will be included in the analysis of the primary and secondary endpoints.

P.3. Analyses of Lead-in Phase

P.3.a. The primary outcome for the Lead-in Phase is the disappearance of HCV RNA. Logistic regression will be used to determine the characteristics that are predictive of a response to peginterferon alfa-2a and ribavirin.

P.4. Analyses of the Primary Outcome

P.4.a. All randomized patients will be included in the analysis of the primary outcome. This includes patients who are later found to be ineligible and patients who do not receive the assigned treatment.

P.4.b. The primary outcome of this trial is progression of liver disease as defined in Section K.

P.4.c. The analysis of this outcome is complicated because this is a composite outcome that consists of both the results of biopsies obtained at two-year intervals and the occurrence of events that may occur at any time during the follow-up period. In addition, the biopsy outcome, the development of cirrhosis, can occur only in patients in stratum 1 (pre-cirrhotic). Patients in stratum 2 will be much more likely to develop clinical events than patients in stratum 1.

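### N.1.d withdraws SAE status from decompensation and HCC in every phase, so a serious non-fatal event before randomization loses its prompt safety report although it lies outside the primary comparison

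*Protocol*

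**What the plan says.** Section N.1.b of the Protocol defines a serious adverse event by the usual criteria, such as death, threat to life and hospitalization. N.1.d then takes a list of liver events out of that definition: "The following events are trial outcomes and will not be considered to be serious adverse events". The list is HCC or presumed HCC, CTP of 7 or higher at two consecutive visits, ascites, variceal hemorrhage, hepatic encephalopathy and SBP. No phase or arm is named.

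N.3.a sets the reporting window. It covers "serious adverse events that occur from the time the patient has signed the Screening or Trial informed consent to study visit Month 54", so it spans screening, the Lead-in and the Week 20 Responder phase. N.1.c makes SAE status a precondition for expediting: "A serious adverse event which is unexpected and is drug related (even remotely) will require expedited reporting".

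On what counts as an outcome, K.1 opens with "The major outcome variable used in this study will be progression of liver disease as judged by any of the following outcomes", again without a phase limit. P.4.a fixes the analysis population: "All randomized patients will be included in the analysis of the primary outcome". P.3.a gives the Lead-in its own endpoint: "The primary outcome for the Lead-in Phase is the disappearance of HCV RNA".

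On exposure, A.2 says of up to 1800 Lead-in patients: "They will be treated with a combination of peginterferon alfa-2a and ribavirin for a period of 24 weeks". Week 20 Responders are treated to Week 48 and followed to Week 72 (I.1.a).

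**The concern.** Exempting efficacy endpoints from SAE reporting is normal when those endpoints are captured and compared elsewhere, and nothing here challenges it for randomized patients. The exemption rests on that capture. Before randomization there is no comparison to capture the event, yet the exemption still applies as written.

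Consider a patient hospitalized for a variceal bleed at Week 14 of the Lead-in. The hospitalization meets N.1.b, but N.1.d cancels it. The patient has no arm, so a by-arm table of outcomes would not show the event, and the patient may never be randomized.

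At stake is how quickly the DCC, the manufacturer and the DSMB learn of hepatic decompensation while everyone is on active drug. The Protocol itself notes, in B.5, that ribavirin hemolysis raises the risk of using that drug in patients with cirrhosis.

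**Working it through.** The Protocol gives no figure for this point, so the check is mainly textual.

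**Step 1. Does the exemption reach the pre-randomization phases?** N.1.d has no phase limit, and N.3.a starts SAE reporting at Screening or Trial consent. Read together, it does.

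**Step 2. Are these events part of the primary comparison before randomization?** K.1 does not say, so the answer comes from other sections.
- P.4.a analyses randomized patients, and O.2.g counts progression over the 3.5 years after randomization.
- P.3.a makes HCV RNA the primary outcome of the Lead-in.
- J.1.c bars randomization after CTP of 7 or higher at two consecutive visits (Weeks 12 and 20 for Lead-in patients) or evidence of HCC on ultrasound. It also bars patients who stopped peginterferon in the Lead-in or responder protocol.
- L.3 ends follow-up at 24 weeks for patients who stop treatment in the Lead-in, except for unresolved adverse events.

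Some of the listed events therefore keep the patient out of the comparison altogether.

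**Step 3. Which reporting routes depend on SAE status?**

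| Route | Section | Needs SAE status? | Reaches a non-fatal listed event before randomization? |
|---|---|---|---|
| 24-hour telephone report to DCC and manufacturer | N.3.a | Yes | No |
| Manufacturer's check for unexpectedness | N.3.a | Yes | No |
| Expedited report to NIDDK, FDA, DSMB and centers | N.1.c, N.3.a | Yes, and must be unexpected and drug related | No |
| Monthly DSMB status report | N.3.a | Yes | No |
| Adverse Event form | N.2.a | No | Yes |
| Annual FDA report | N.3.a | No | Yes |
| Death report | N.3.b | No | No; fatal events only |
| Outcome Review Board | Q.1.j | No | Possibly; no phase stated, adjudication only |
| DSMB monitoring of low-count entrants | H.1.e, Appendix D4 | No | That subset, first 8 weeks only |

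For patients not yet treated, N.3.a asks for a report to the DCC alone. In screening the loss is therefore smaller than on treatment.

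**Step 4. Does any section restore the lost routes?** None does. The interim report contents in P.5.b list recruitment, baseline tables and violations, with no table of Lead-in decompensation.

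**Step 5. Scale.** Inputs from the Protocol are a ceiling of 1800 Lead-in patients, 24 weeks of treatment (A.2) and about 20% Week 20 Responders (B.6), who have 24 further weeks to Week 48. The decompensation rate of 1–3% per year is an assumption; the Protocol gives none for these phases.
- Lead-in: 1800 × 24 / 52.18 = 827.9 person-years; × 1% to 3% = 8.3 to 24.8 events.
- Responders: 0.20 × 1800 = 360; 360 × 24 / 52.18 = 165.6 person-years; × 1% to 3% = 1.7 to 5.0 events.
- Together: about 10 to 30 events at the ceiling.

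If Lead-in enrollment were only what 900 randomized patients require at 20% response, 900 / 0.80 = 1125 patients. That gives 1125 × 24 / 52.18 = 517.4 person-years and 5.2 to 15.5 events. The 225 responders add 103.5 person-years and 1.0 to 3.1 events.

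These counts include every decompensation and assume full 24-week exposure. Only those meeting N.1.b would have been SAEs. Ascites seen only on ultrasound, or a CTP of 7 driven by laboratory values, might not qualify.

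**The case against.** A reader might infer that, but for N.1.d, each of these events would have been expedited. The documents do not support that. N.1.c also requires the event to be unexpected and drug related, and Section B.1 describes decompensation and HCC as the natural course of the disease. What stands is narrower: the manufacturer's check for unexpectedness applies to SAEs, so it is never made for these events.

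A reader might also infer that the listed events are outcomes only in randomized patients. K.1 does not say so. N.3.b sends deaths to the Outcome Review Board from Trial consent onward, so for deaths at least the outcome pathway runs before randomization. Q.1.j has the Board review all Section K events without a phase limit, so non-fatal Lead-in events may reach it. This limits the claim that the events go unexamined. It does not supply a prompt safety report, because the Board only adjudicates.

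Nor does every patient in these phases take full doses of both drugs. Low-count entrants start on a reduced peginterferon dose, ribavirin-intolerant patients may take peginterferon alone (H.1.d, H.1.e), and responder dosing is at the investigator's discretion (I.4.b). The point holds for peginterferon with or without ribavirin.

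The population is also selected for lower risk. F.2 and F.3 exclude CTP of 7 or higher, any history of ascites or encephalopathy, and prior variceal bleeding, while non-cirrhotic patients are admitted. The true rate may be below the assumed range. The DSMB also reviews data at regular intervals (Q.1.i), although no section says that these events are put before it.

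Finally, this version ends randomized treatment in January 2007. Counting back 42 months gives July 2003, so Lead-in treatment was probably complete for most patients. That weakens the prospective value of a change but leaves the rule as written unsound.

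**Conclusion.** The concern holds in a limited form. As written, N.1.d applies in phases where the events it exempts are not part of the primary comparison. A non-fatal event there that would otherwise meet N.1.b loses the 24-hour report, the check for unexpectedness, any expedited report that might follow from it, and the monthly DSMB SAE status report.

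This rests on reading the limit of the primary comparison from O.2, P.3.a, P.4.a and J.1.c, since K.1 is silent. The size cannot be fixed from the document. The 10 to 30 decompensations are an illustrative count at an enrollment ceiling and an assumed rate. The number of SAEs lost is an unknown subset. The textual gap does not depend on that number. It is a safety-reporting rule that should be corrected, and it does not bear on the validity of the randomized comparison.

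**What to change.** Limit N.1.d to events after randomization, for example by opening it with the words: in randomized patients. Add one sentence stating that the same events during screening, the Lead-in and the Week 20 Responder phase are SAEs when they meet N.1.b, and follow N.1.c and N.3.a. State in K.1 or Q.1.j whether pre-randomization events also go to the Outcome Review Board.

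The cost is a sentence or two, a note to sites and a modest number of additional SAE forms. If the Lead-in and responder phases are already complete, the same rule can be applied to the Adverse Event forms on file, so that events meeting N.1.b are listed for the DSMB.

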## **O. SAMPLE SIZE**

### **O.1. Estimates of rates for the primary outcome variable**

O.1.a. The primary outcome variable for the trial will be the progression of liver disease as judged by either:

1. An increase in the Ishak fibrosis score of 2 points or more at the study\_visit month 24 or study visit month 48 biopsies, or
2. The development of hepatic decompensation (as defined in K.1.), the development of HCC, or death from any cause.

### **O.2. Sample size estimate**

O.2.a. The primary variable for this trial is the percent of patients whose liver disease has progressed (as defined in K.1.) at the time of the biopsy at study visit month 48. The sample size estimate is based on a chi-square test (171).

O.2.b. The null hypothesis is that the percent of patients with progression of liver disease will be the same in the peginterferon alfa-2a treated and control arms. The alternative hypothesis is that there will be at least a 50% reduction in the annual rate of progression in the peginterferon alfa-2a arm when compared to the control arm.

O.2.c. The sample size is based on a two-sided alpha (type I error) of 5% and a power of 90% (type II error).

O.2.d. If the annual rate of progression of liver disease is  $p$ , then the rate at the end of 3.5 years is calculated as:

$$1 - (1-p/2) * (1-p) * (1-p) * (1-p).$$

O.2.e. Noncompliance rates of 3%, 6%, and 9% have been assumed for the peginterferon alfa-2a arm in years 2, 3, and 4. These patients will continue to be followed and will experience progression at the rate of the control arm.

O.2.f. Similarly, it is assumed that 5%, 10% and 15% of the control arm will elect to be treated and will receive peginterferon alfa-2a in years 2, 3 and 4. These patients will continue to be followed and will experience progression at the rate of the peginterferon alfa-2a arm.

O.2.g. Under these assumptions, 18.7% of the control arm and 10.6% of the peginterferon alfa-2a arm will have had progression of their liver disease 3.5 years after randomization. A sample size of 810 patients (405 per arm) will have 90% power to detect this difference. Nine hundred patients will be randomized for this trial, allowing for a loss to follow-up of 90 patients.

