## **E. INCLUSION CRITERIA**

Patients can be screened for the HALT-C Trial as either “Lead-in” or “Express” patients. Lead-in patients are treated for 24 weeks with peginterferon alfa-2a and ribavirin as part of the HALT-C Trial. Patients who have been treated with peginterferon and ribavirin outside of the HALT-C Trial can bypass the Lead-in Phase and be randomized as “Express” patients.

Sections E1, E2, E5, E8, and E9 are for all patients. Sections E3, E4, and E6 are for “Lead-in” patients and E7 is for “Express” patients.

- E.1. Age at entry at least 18 years.
- E.2. HCV-RNA positive or serology positive for HCV antibody by a second generation or higher assay.
- E.3. Lead-in patients must have had previous treatment with any interferon preparation (standard or pegylated interferon), utilized either alone or in combination with ribavirin, administered at a minimum dose of 3 mU three times weekly or its equivalent, for at least 12 weeks. No interferon, ribavirin, or amantadine treatment in the 2 months prior to screen visit #1.
- E.4. Lead-in patients: Documented non-response to the most recent adequate course of interferon therapy, as defined in E.3. Non-response will be defined as follows:
- E.4.a. A positive test for HCV RNA after at least treatment week 12 of adequate interferon therapy while still being treated, or within one week of discontinuing the most recent adequate course of interferon.
- E.4.b. If virologic measurements were not performed or are unavailable from the most recent adequate treatment, serum ALT must have been elevated within 6 months of onset and at anytime during 4 weeks prior to or 1 week after stopping this prior adequate course of interferon therapy.
- E.4.c. If elevated serum ALT's or positive HCV-RNA laboratory test are not available, a clinical note documenting non-response will suffice.
- E.5. A positive test for HCV RNA, by the Core Virology Laboratory, at the time of screening to enter the study.
- E.6. Lead-in patients must satisfy the following biopsy criteria:

E.6.a. Patients selected to enter the HALT-C Lead-In Phase, must have had a liver biopsy performed at least 2 months following the last course of interferon and within 12 months prior to the baseline visit, demonstrating at least Ishak stage 3 fibrosis as judged by the clinical center pathologist.

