E. 6. b. Patients with a history of Ishak stage 3 or higher fibrosis, who subsequently have fibrosis scored as Ishak 2 can also be enrolled. Both biopsies must be read by the local HALT-C pathologist using the Ishak fibrosis scoring system. The most recent Ishak fibrosis score will be used for determination of the study outcome.

E.7. Express patients: Documented adequate pegylated interferon and ribavirin for at least 24 weeks may be substituted for the Lead-in Phase of the study provided the following criteria are met:

E.7.a. adequate drug dosing is defined as follows:

1. intent to treat with

a. peginterferon alfa-2a 180 mcg/wk or peginterferon alfa-2b 1.5 mcg/kg/wk

AND

b. 800 mg daily of ribavirin (minimum)

2. Dose adjustment is dependent on patient's tolerance to the drug(s) and is at the discretion of the treating physician. (see H.1.d. and I.4.b.)

E.7.b. A positive HCV-RNA obtained at least 20 weeks after the start of the adequate course of treatment with pegylated interferon with ribavirin and before Screening for HALT-C. This test may be obtained either on or off treatment.

E.7.c. A pre-treatment liver biopsy which is available and has been performed within 18 months of randomization or a liver biopsy which is performed at least 8 weeks after the end of treatment and no more than 24 weeks prior to randomization. Slides from the biopsy must demonstrate at least Ishak stage 3 fibrosis as judged by the clinical center pathologist and then must be read centrally before randomization.

E. 7. d. Patients with a history of Ishak stage 3 or higher fibrosis, who subsequently have fibrosis scored as Ishak 2 can also be enrolled as Express patients. Both biopsies must be read by the local HALT-C pathologist using the Ishak fibrosis scoring system. The most recent Ishak fibrosis score will be used for determination of the study outcome.

E. 8. A willingness by all women of child bearing potential to utilize adequate contraception during the Main Trial study. Use of adequate contraception is not mandated during the extension trial since no medication is being offered.

E.9. A willingness by all men to utilize adequate contraception during the time they are treated with interferon-ribavirin combination therapy and for 6 months thereafter.

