## **J. RANDOMIZED PHASE**

### **J.1. Assessment for Randomization**

J.1.a. Patients who do not have a virologic response may be assessed for randomization at the following times:

1. between weeks 20 and 24 for those who have gone through the Lead-in Phase,
2. during Screening for the Express patients,
3. at weeks 36, 48, 60 or 72 for Week 20 Responders. Any virologic breakthrough or relapse must be confirmed by a blood draw on a separate day. Patient must be willing to be re-biopsied if their baseline (Screening) biopsy is greater than 30 months from the time of Breakthrough/Relapse Randomization.
4. After Week 72, a W20 Responder HALT-C patient who relapses may be re-screened as an Express patient.

J.1.b. The investigator will confirm the patient's eligibility for randomization, as follows:

1. A serum sample will be drawn and sent to the Virology Core Laboratory (via the Central Repository) for determination of HCV RNA.
2. AFP determination and Ultrasound examination of the liver will be performed for HCC Screening.
3. Laboratory tests, including liver chemistries, routine chemistries, CBC, TSH, and PT will be obtained.
4. Calculation of Child-Turcotte-Pugh score.
5. Willingness to participate in the trial for 4 years after randomization.

J.1.c. Patients with detectable HCV RNA at weeks 20, 36, 48, 60 or 72 and during Screening for Express patients will not be eligible for the Randomized Phase if they have any of the following:

1. elevation of serum alpha-fetoprotein greater than 1000 ng/mL
2. evidence of HCC on ultrasound
3. Child-Turcotte-Pugh score greater than or equal to 7 at 2 consecutive visits:
  - week 12 and week 20 for those patients entering through the Lead-in Phase
  - 2 separate Screening visits for Express patients
  - Weeks 36, 48, 60, 72 for Week 20 Responders
4. unwillingness to repeat a baseline (Screening) biopsy which is greater than 30 months from time of Breakthrough/Relapse Randomization. This biopsy must be read by the Central Pathology for stratification of Randomization.

Patients who discontinue peginterferon alfa-2a treatment during the Lead-in Phase or during treatment in the parallel responder protocol are not eligible to be randomized. (see L.3.)

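### The power calculation counts progression from randomization, but the Ishak component is measured from an earlier entry biopsy, so the stated 90% holds only if almost no fibrosis progression occurs in between

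*Protocol*

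**What the plan says.** Protocol O.2.a takes as the primary variable the percentage of patients who have progressed, as defined in K.1, by the Month 48 biopsy. "The sample size estimate is based on a chi-square test". O.2.b assumes that "there will be at least a 50% reduction in the annual rate of progression in the peginterferon alfa-2a arm". O.2.d compounds the annual rate over half a year plus three full years. O.2.g dates the result: "18.7% of the control arm and 10.6% of the peginterferon alfa-2a arm will have had progression of their liver disease 3.5 years after randomization". The clock therefore starts at randomization, and the arms differ throughout.

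The histologic component in K.1.a is: "Increase in Ishak fibrosis score by 2 points or more at 2 or 4 year biopsies". It does not say which biopsy the increase is measured from. Four other places point to the entry biopsy:

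- P.2.a collects baseline data before the Lead-in, or before treatment starts for Express patients.
- J.1.d stratifies on the central reading of the screening biopsy, or of the most recent biopsy for Breakthrough/Relapse patients.
- E.6.b and E.7.d use the most recent entry score for the outcome in patients later read as Ishak 2.
- Table 1 schedules no liver biopsy at Week 24.

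The entry biopsy can be old at randomization. For Lead-in patients (E.6.a) it is taken "within 12 months prior to the baseline visit, demonstrating at least Ishak stage 3 fibrosis as judged by the clinical center pathologist", and 24 weeks of Lead-in follow. For Express patients (E.7.c) one option is: "A pre-treatment liver biopsy which is available and has been performed within 18 months of randomization". The other is a post-treatment biopsy at most 24 weeks old. For Breakthrough/Relapse patients (J.1.a item 3): "Patient must be willing to be re-biopsied if their baseline (Screening) biopsy is greater than 30 months from the time of Breakthrough/Relapse Randomization".

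**The concern.** The endpoint and the formula use different windows. An Ishak rise between the entry biopsy and randomization counts as an outcome under K.1.a, yet it arose before the arms differed. Such events are expected equally in both arms. They raise both percentages, pull the risk ratio toward 1, and lower the power of the comparison for which 405 per arm was chosen.

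Section O has no allowance for this. The 3-month rows of O.3 assume that pre-randomization treatment protects the control arm for a time after randomization. That lowers control-arm events; it does not add events common to both arms. O.3 treats that 3-month shift as worth tabulating (90% falls to 86%), and the interval left out here is usually longer.

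**Working it through.** **1. Age of the reference biopsy at randomization.** Taking 24 weeks as 24/4.345 = 5.5 months:

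| Route | Biopsy age at randomization |
|---|---|
| Lead-in | 0 + 5.5 to 12 + 5.5, so about 5.5-17.5 months |
| Express, pre-treatment biopsy | up to 18 months |
| Express, post-treatment biopsy | at most 24 weeks |
| Breakthrough/Relapse | up to 30 months |

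The 30-month re-biopsy trigger is seldom met: 12 months plus 72 weeks is 12 + 72/4.345 = 28.6 months.

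**2. Reproducing O.2.g.** Inputs are 6% and 3% per year, crossover of 5/10/15% in the control arm and noncompliance of 3/6/9% in the peginterferon arm in years 2-4 (O.2.e, O.2.f), and 405 per arm.

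- Control: 1 − 0.97 × 0.9415 × 0.943 × 0.9445 = 18.66%.
- Peginterferon: 1 − 0.985 × 0.9691 × 0.9682 × 0.9673 = 10.60%.
- Two-proportion power at two-sided 5%: 0.902.

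All nine power values in O.3 reproduce within 2 points from the printed rates.

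**3. Adding the pre-randomization interval.** The protocol gives no figure for three inputs, so they are assumptions:

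- h: the histologic share of the 6% annual rate, 0.3-0.7.
- T: biopsy age at the Lead-in baseline, 0-1 year.
- k: progression during the Lead-in (taken as 0.5 year) relative to the untreated rate, from 0 (fully protective) to 1 (not protective).

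*Model A, pure dilution.* Multiply the event-free probability in both arms by (1 − 0.06h)^T × (1 − 0.06hk)^0.5. For h = 0.5, T = 0.5, k = 1, the factor is 0.97^0.5 × 0.97^0.5 = 0.97. Control becomes 1 − 0.8134 × 0.97 = 21.1%, peginterferon 1 − 0.8940 × 0.97 = 13.3%, and power 0.84.

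*Model B, two steps.* K.1.a needs 2 points, so a patient may gain one point before randomization and one after. Let one-point steps follow a Poisson process with mean m, so that histologic event-free probability is e^(−m)(1 + m). Calibrate m in each arm so that, with no prior interval, 18.66% and 10.60% are recovered, and leave the clinical part, S^(1−h), unchanged (S = the arm's event-free probability in step 2). For h = 0.5, m is 0.526 (control) and 0.373 (peginterferon). The control step rate is 0.526/3.5 = 0.150 per year. With T = 0.5 and k = 1, 0.150 is added to both means, giving 23.1% vs 14.7% and power 0.87.

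| h | T (months) | Power, model A (k = 1 to 0) | Power, model B (k = 1 to 0) |
|---|---|---|---|
| 0.3 | 0 | 0.88-0.90 | 0.89-0.90 |
| 0.3 | 12 | 0.85-0.87 | 0.87-0.88 |
| 0.5 | 0 | 0.87-0.90 | 0.89-0.90 |
| 0.5 | 6 | 0.84-0.87 | 0.87-0.89 |
| 0.5 | 12 | 0.81-0.84 | 0.85-0.87 |
| 0.7 | 0 | 0.86-0.90 | 0.88-0.90 |
| 0.7 | 12 | 0.77-0.81 | 0.83-0.86 |

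The overall range is 0.77-0.90 under A and 0.83-0.90 under B. Power stays at 0.902 only when T = 0 and k = 0.

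**The case against.** Much of the opposing case stands.

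- The printed figures contain no arithmetic error, and O.2.d-g state their window openly. A reader might infer a miscalculation; there is none. The problem is that the formula's window is not the endpoint's.
- The size of the loss rests on inputs that the protocol does not give. A reader might push the calculation to h = 1, where model A falls to 0.71. The protocol does not support that case: P.4.c confines the biopsy outcome to the pre-cirrhotic stratum and expects more clinical events in the other, and K.1 lists seven non-biopsy outcomes.
- A fully protective Lead-in cannot be excluded, since O.3 itself considers protection from pre-randomization treatment. With a fresh biopsy there is then no loss.
- Pure dilution overstates the effect for a 2-point threshold. Model B roughly halves the loss in the central case.
- The 30-month figure is a ceiling. The protocol gives no share of Breakthrough/Relapse patients, and those patients had undetectable HCV RNA at week 20, so that interval is left out of the power range.
- O.3 already shows power from 73% to 96%. Those rows vary the annual rate, noncompliance and control-arm carry-over, however; none represents progression common to both arms before randomization.
- P.4.d leaves the interval-censored method to the Manual of Operations, so its full specification is not missing. Where the histologic interval starts still has to agree with the endpoint.

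**Conclusion.** The point holds as a mismatch between the endpoint's window and the window in the power calculation. The 90% in O.2.g is right for progression that starts at randomization. For the K.1 outcome it requires that essentially no 2-point histologic progress accrues between the reference biopsy and randomization.

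For h = 0.3-0.7, T = 0-12 months and k = 0-1, power at 405 per arm is about 77-90% under pure dilution and about 83-90% if straddling rises stay treatable. In the central case (h = 0.5, T = 6 months) it is about 84-89% across both models. The protocol does not support any single replacement figure.

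A reader might also infer that the treatment comparison is biased. It is not: events before assignment are expected equally in both arms, so validity under the null is unaffected. What is at stake is power and the dilution of the estimated effect.

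**What to change.** 1. In K.1.a, name the biopsy from which the 2-point increase is measured for each entry route: Lead-in, Express with a pre-treatment or post-treatment biopsy, and Breakthrough/Relapse with or without re-biopsy.
2. Add rows to O.3 and one sentence to O.2.g giving power over a stated range of pre-randomization histologic progression common to both arms. State the assumed histologic share, biopsy age and Lead-in effect. Give a range, not one new figure.
3. In the interval-censored analysis of P.4.d, or in the Manual of Operations text to which it refers, start the histologic interval at the reference biopsy date, with a common hazard until randomization and a treatment effect only afterwards.

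The cost is a rerun of the power table and a few sentences. No additional biopsy or patients are needed. The downside is that the stated power becomes slightly less favourable.
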